### 3.3 Circulating factors

Forty mL of blood will be taken from patients and centrifuged for 10 minutes at 1600 RPM or 15 minutes at 2500 RCF for separation of serum and plasma, respectively. Five, 500 μL samples of serum and plasma are aliquoted for each patient and samples are stored in a -80° freezer awaiting analysis of antioxidant capacity, cytokine levels, and endothelial biomarkers.

#### 3.3.1 Hydroxyl radical antioxidant capacity assay (HORAC)

Reactive oxygen species (ROS) have deleterious effects on the vascular endothelium [91]. Hence, antioxidant capacity is critical in combatting these insults and maintaining a healthy endothelium. Clinical and preclinical models have demonstrated that aging impairs NVC, and with the aid of antioxidant agents, can rescue NVC response [37] and improve cognition [92]. Importantly, elevations in oxidative stress are associated with patients who have recovered from COVID-19 and correlate with neuropsychiatric impairment [93]. Specifically, a recent meta-analysis showed an elevated oxidative stress/antioxidant ratio in MCI patients compared to healthy controls [94] and elevation of peripheral markers of oxidative stress in MCI, AD and VaD have been reported [95].

The antioxidant capacity of the serum samples will be measured using the Hydroxyl Radical Antioxidant Capacity (HORAC) Assay (Cell Biolabs, Inc., San Diego, CA). This 96-well plate-based assay contains a fluorescent probe which is quenched by hydroxyl radicals generated by the addition of a hydroxyl radical initiator and fenton reagent to the samples. The antioxidants present in the sample will neutralize the hydroxyl radicals and prolong the life of the fluorescent probe. Hence, more the antioxidants in the sample, the longer it takes for the complete decay of the fluorescent probe. Briefly, 20ul of the gallic acid standards or samples are added to the wells, followed by addition of 1X fluorescein solution and incubation at room temperature for 30 minutes. Then, hydroxyl radical initiator and the fenton reagent are added to the wells. After briefly shaking the plates for uniform mixing, the fluorescence will be measured in increments of 5 minutes for 1 hour using Tecan Spark multimode microplate reader. The fluorescence decay curve, represented as the area under the curve (AUC) is compared against the standard gallic acid antioxidant curve to calculate the antioxidant capacity of the serum samples fluorometrically. This measure has been previously validated in serum of patients with age-related diseases and correlates to functional measures [96].

#### 3.3.2 Magnetic bead-based multiplex assay

Circulating inflammatory cytokines and biomarkers of endothelial dysfunction present in the sera and plasma will be measured by Bio-Plex 200 System magnetic bead-based multiplex assay (Bio Rad, CA). A Milliplex Human Adipokine Magnetic Bead Kit (EMD Millipore, Billerica, MA) will be used to determine cytokines of interest: Tumor necrosis factor alpha (TNF-alpha), interleukin-1 beta (IL-1b), interleukin-6 (IL-6), interleukin-8 (IL-8) and interleukin-10 (IL-10). Multiple research groups have demonstrated that COVID-19 is associated with long-lasting elevations in inflammation that persist for at least 10-months after infection [97–99]. Importantly, elevations in pro-inflammatory cytokines are associated with systemic endothelial dysfunction in aging [100] and dementia [101]. A Milliplex Human Cardiovascular Disease Panel 1 Kit (EMD Millipore, Billerica, MA) will be used for myeloperoxidase (MPO), matrix metallopeptidase 9 (MMP-9), E selectin, vascular cell adhesion molecule-1 (VCAM-1), intercellular cell adhesion molecule-1 (ICAM-1), and plasminogen activity inhibitor-1 (PAI-1). Immunofluorescence signals will be quantified (pg/ml) and compared between groups. Growing evidence points towards endothelial impairment as a key mediator in the progression from cognitive decline to dementia. Molecules represented in the cardiovascular disease panel have been reported as biomarkers of endothelial dysfunction in vascular diseases [102] and dementia [103]. Additionally, higher levels VCAM-1 and ICAM-1 were able to differentiate AD vs MCI [104].

### 3.4 Data management

To enhance confidentiality and security, information is saved on computers that are password-protected and encrypted. Each participant is allocated an exclusive anonymous identifier that is associated with all data collected, such as questionnaires, NIH toolbox, and NVC assessment. Medical health information and demographics are collected using Redcap. Paper records, including consent form are kept in a locked, secure area that is only accessible to the research team.

### 3.5 Safety consideration

Overall, the procedures utilized in this study are associated with minimal risks that are typically associated with routine medical examinations and testing. However, there are rare potential risks involved in some procedures. For the eye examination, there is a possibility that flickering light could trigger a seizure if the participant has photosensitive epilepsy and dilating the pupils may lead to an acute glaucoma attack in patients with shallow anterior chamber depth and/or elevated intraocular pressure in rare occasions. Therefore, all participants will undergo an extensive medical questionnaire and have the eyes tested before the dilation process (eye pressure and anterior chamber depth). If history of seizures is present or high eye pressure and small anterior chamber is recorded, the participant will not be eligible for dynamic retinal vessel analysis examination. Additionally, dilation of the pupils may cause impaired vision for a few hours after the procedure, so it is advised that participants have someone drive them home on the day of their visit. As part of this study, venipuncture (blood draw) will be performed. Some risks associated with this procedure include pain from the needle insertion, discomfort from pressure and cold application (if necessary), bruising, feeling faint, and a slight risk of infection.

### 3.6 Ethical issues

The current investigation adheres to the principles outlined in the Declaration of Helsinki and has been granted ethical approval by the institutional review board (IRB) of OUHSC and VA, under protocol number 14585. Prior to participation, individuals will provide written informed consent by signing a statement of agreement. Participants are free to withdraw from the study at any time without consequence. In instances where a participant is unable to provide consent, a substitute written consent from a designated family member or caregiver will be accepted. Respect for each participant’s personal beliefs will be taken into consideration, and all individuals must provide their assent to the research protocol. Given the progressive and ongoing nature of the illness being studied, the capacity for consent may need to be periodically reevaluated, and this will be done on an as-needed basis.

### 3.7 Length of study

Participant enrollment for this study is expected to take 2 years, allowing for baseline physiological, cognitive, circulating factors, and neuroimaging data from up to 200 patients. Each patient will undergo a second visit and MRI 18-months following their baseline visit, bared an early termination or drop-out. Follow-up measurements are expected to conclude in 2026.

## 4. Statistical analysis

### 4.1 Cross-sectional data analysis

Upon testing for normality of continuous data, independent t-test or Mann-Whitney *U* Test will be used for group comparison (COVID+ vs COVID-) and Chi-square or Fisher’s exact test for group comparison of categorical variables. Effect size will be calculated for all within and between group analyses. For **primary outcome** analysis, testing whether COVID-19 impairs NVC responses in MCI patients, fNIRS data will be analyzed using a pipeline based on General Linear Model (GLM) approach created using the Brain AnalyzIR toolbox. At the first (subject) level, regression (β) coefficients characterize NVC response and will be estimated for channels of interest in the prefrontal cortex across all n-back blocks and chromophores (HbO and HbR). At the second (group) level the GLM treats COVID status as an independent categorical factor, while the n-back block as a repeated measures factor and yields corresponding *t*-contrasts comparing NVC response within and between groups. We will test whether demographic variables, COVID-19 variants, duration of COVID-19 and vaccination influences the primary outcome through linear regression. Moreover, we will create a multivariate model using β coefficients, generated from the fNIRS pipeline, to determine whether COVID-19 predicts impairment in NVC in MCI patients. Univariate analyses of factors that may contribute to NVC impairment (i.e., age, sex, baseline structural MRI abnormalities) will be conducted, and analyses with a p value of <0.2 will be included in the multivariate model. **Secondary outcome** measures (i.e., FMD, LSCI, EEG, DVA, NIH Toolbox, circulating factors) will be compared between groups. Additionally, we will determine whether history of COVID-19 contributes to impairment in functional cognitive measures (i.e., n-back, NIH Toolbox) by multiple and simple linear regression. For **exploratory analyses**, we will determine whether group (COVID+ vs COVID-) alters the relation between NVC and peripheral, cognitive, and structural measures through multiple regression. Correlations for these variables will be performed within groups to determine strength of relationship with NVC.

### 4.2 Longitudinal data analysis

Continuous data will be analyzed by 2-way ANOVA and categorical with Chi-square or Fisher’s exact test for within and between groups (COVID+ vs COVID-) comparison. Effect size will be calculated for all within and between group analyses. For **primary outcome** analysis, we will determine whether COVID-19 related impairment in NVC and increases in WMH burden contributes to progression to dementia. Progression to dementia within and between groups will be analyzed and multivariate analysis will be conducted to determine the effect of COVID-19, NVC (i.e., fNIRS), change in WMH burden, and interaction between group (COVID+, COVID-) and NVC and WMH burden on progression to dementia. **Secondary outcome** measures (i.e., FMD, LSCI, EEG, DVA, NIH Toolbox, circulating factors) will be compared within and between groups. Demographic variables, COVID-19 variants, duration of COVID-19 and vaccination will be assessed as factors for progression to dementia through logistic regression. **Exploratory analyses** will include univariate analysis of all demographics, physiologic, cognitive, and structural variables, and their effect on progression to dementia. All values with a p value <0.2 will be included in a multivariate model to assess their contribution to progression to dementia. We expect that several variables will have p value <0.2; therefore, we will conduct dimensionality reduction before adding into the model to assess variables which have strongest correlation with principal components. The limitation for the multivariate model will be sample size, however this is not a primary outcome measure and is used to generate new hypotheses to test in future studies.

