**Methodology:**

A prospective longitudinal study is conducted at the University of Oklahoma Health Sciences Center. Patients are screened in the Department of Neurology and must have a formal diagnosis of MCI, and MRI imaging prior to study enrollment. Patients who meet the inclusion criteria are enrolled and followed-up at 18-months after their first visit. Visit one and 18-month follow-up will include an integrated and cohesive battery of vascular and cognitive measurements, including peripheral endothelial function (flow-mediated dilation, laser speckle contrast imaging), retinal and cerebrovascular hemodynamics (dynamic vessel retinal analysis, functional near-infrared spectroscopy), and fluid and crystalized intelligence (NIH-Toolbox, *n*-back). Multiple logistic regression will be used for primary longitudinal data analysis to determine whether COVID-19 related impairment in neurovascular coupling and increases in white matter hyperintensity burden contribute to progression to dementia.

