### 2.2 Study design

This study will test the hypothesis that COVID-19 infection promotes systemic endothelial dysfunction, impairing NVC responses and promoting white matter damage, contributing to the progression of MCI to dementia. To test this hypothesis, we will prospectively follow patients, who are diagnosed with MCI, with or without history of SARS-CoV-2 infection, for 18 months. The timeline for study design and investigative measurements are represented in **Fig 1.** Study participants will be evaluated for eligibility and enrolled through neurology clinics at the University of Oklahoma Health Sciences Center (OUHSC) and Oklahoma City Veterans Affairs (VA) Medical Center (Visit 0). Upon enrollment, patient history, demographic data, standard risk factors for dementia, cognitive status and WMH status (MRI scan) will be recorded. Blood collection, cognitive tests (NIH-toolbox, *n-*back), and baseline physiologic assessments for peripheral endothelial function (flow-mediated dilation [FMD], laser speckle contrast imaging [LSCI]) and NVC responses (functional near-infrared spectroscopy [fNIRS], dynamic retinal vessel analysis [DVA]) will be conducted at the OUHSC Translational Geroscience Laboratory (Visit 1). Study participants will undergo semi-annual clinical neurologic evaluations as a part of standard care. In addition to COVID-19 status since enrollment (e.g., PCR+/-, symptoms), progression from MCI to dementia will be assessed by the clinical neurology team with final adjudication made through consensus management conferences. Repeat of all physiological assessments, cognitive tests, and serum collection will be performed at month 18 (Visit 2), and the second MRI scan will be performed. If some participants decide to terminate their participation in the study for any reason, they will be invited to an early termination visit, which will include the same evaluations as in Visit 2.

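### Section 4.2 names unpaired chi-square or Fisher tests for within-group comparison over time, and does not make visit a within-patient factor in its 2-way ANOVA

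*Protocol article*

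**What the plan says.** **Data structure.** Under section 2.2 of the protocol article, the physiological, cognitive and serum measures taken at Visit 1 are repeated in the same patients at month 18, and a second MRI is done. Section 3.7 confirms this: "Each patient will undergo a second visit and MRI 18-months following their baseline visit". The first MRI is the scan made at diagnosis of MCI (sections 2.7 and 2.10).

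**Tests for these data.** Section 4.2 opens with: "Continuous data will be analyzed by 2-way ANOVA and categorical with Chi-square" or Fisher's "exact test for within and between groups (COVID+ vs COVID-) comparison". It later says that the secondary outcomes (FMD, LSCI, EEG, DVA, NIH Toolbox, circulating factors) "will be compared within and between groups". The section names no paired test, subject effect, mixed model or repeated-measures factor for visit.

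**Contrast with the cross-sectional plan.** Section 4.1 does name such a factor for the fNIRS model, which treats COVID status as independent, "while the n-back block as a repeated measures factor".

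**Primary longitudinal analysis.** The abstract gives a different method for this: "Multiple logistic regression will be used for primary longitudinal data analysis".

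**The concern.** Two observations on one person are correlated, and a test that assumes independent observations uses the wrong variance for them.

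For categorical data the text itself assigns such a test to the within-group comparison. A natural candidate is the presence of microbleeds (section 3.1.2). Fazekas grade is another, if it is handled as categorical.

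For continuous data the text leaves open whether the ANOVA accounts for the pairing. An analyst who followed the sentence literally could fit group and visit as two ordinary between-subject factors. The errors would then run in opposite directions. Tests of change, and of whether change differs by COVID-19 history, would lose power. The overall group difference would be declared too often. A reader of the results could not tell which way a given p-value was off without knowing which model had been fitted.

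**Working it through.** No figure stated in the protocol depends on this choice, so there is none to reproduce. The protocol gives no correlation between visits; the values of r below are assumptions.

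**1. Categorical data, within one group**

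Illustrative counts (assumed) for 85 patients with a binary finding at two visits: 24 positive at both, 2 positive then negative, 11 negative then positive, 48 negative at both. Visit 1 has 24 + 2 = 26 positive (30.6%). Visit 2 has 24 + 11 = 35 positive (41.2%).

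- Chi-square, treating the visits as 170 separate people: 170 × (26×50 − 35×59)² / (85 × 85 × 61 × 109) = 2.07, p = 0.150.
- Fisher's exact test on the same table: p = 0.201.
- Exact McNemar, using the 2 + 11 = 13 discordant pairs: 2 × (1 + 13 + 78) / 2¹³ = 184/8192, p = 0.022.

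The unpaired tests ignore that most patients do not change. With positive correlation between visits they are too conservative.

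**2. Continuous data, if the ANOVA is unpaired**

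Take equal variance σ² at each visit, correlation r, and group sizes n₁ and n₂.

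- Group-by-visit contrast (difference in mean change). True variance is 2σ²(1−r)(1/n₁+1/n₂). The unpaired model uses 2σ²(1/n₁+1/n₂). The SE is overstated by 1/√(1−r), and the same factor applies to the visit effect.
- Group contrast averaged over visits. True variance is σ²(1+r)/2 × (1/n₁+1/n₂). The unpaired model uses σ²/2 × (1/n₁+1/n₂). The SE is understated, by a factor 1/√(1+r).

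At two-sided 5%, for an effect that a paired analysis detects with 80% power (1.96 + 0.84 = 2.80 standard errors):

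- Power of the unpaired group-by-visit test = Φ(2.80 − 1.96/√(1−r)).
- Its type I error = 2[1 − Φ(1.96/√(1−r))].
- Type I error for the group effect = 2[1 − Φ(1.96/√(1+r))].

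| Assumed r | SE ratio, change and group-by-visit | Type I error, group-by-visit | Power (80% if paired) | Type I error, group effect |
|---|---|---|---|---|
| 0.3 | 1.20 | 1.9% | 68% | 8.6% |
| 0.5 | 1.41 | 0.56% | 51% | 11.0% |
| 0.7 | 1.83 | 0.035% | 22% | 13.3% |
| 0.9 | 3.16 | about 0 | about 0 | 15.5% |

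A simulation (85 per group assumed, 10,000 runs) agrees. At r = 0.5, type I error was 0.6% for group-by-visit and 10.7% for group. At r = 0.7, it was 0.05% and 13.8%.

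**3. Continuous data, if the ANOVA is repeated-measures**

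The error terms respect the pairing. Type I error returns to 5% and power to 80%, so every entry above becomes irrelevant.

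**4. Reach**

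Progression to dementia is one binary outcome per patient. Section 2.6 excludes dementia at entry, so it has no paired baseline. The logistic regression is not touched. In the section 4.2 model, WMH enters as a change score, which already uses the pairing.

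**The case against.** **The ANOVA wording may be shorthand.** Section 4.2 does not name the two factors and does not call the model between-subjects. Authors often write 2-way ANOVA for a two-way repeated-measures or mixed ANOVA, which is valid for two visits. Section 4.1 shows that the authors know repeated measures, and it also speaks of within- and between-group comparison for a model with a repeated factor. A journal article condenses a fuller plan. This stands: a reader might infer that the continuous analyses treat the two visits as separate people, but the text does not establish it.

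**Completers and early termination.** A reader might also infer that patients without Visit 2 will be dropped, or that early assessments will be counted as month 18. Section 2.2 says only that those who leave "they will be invited to an early termination visit, which will include the same evaluations as in Visit 2". No rule for either case is stated, and handling of missing visits is commonly left to the analysis plan. Neither inference is supported.

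**Fazekas grade may not go to chi-square.** Table 1 lists it as discrete, apart from the nominal and binary variables. That stands as a caution about the example. It does not rescue the sentence, which assigns chi-square or Fisher's test to within-group comparison of any categorical measure.

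**The inflated group effect is not a stated hypothesis.** Section 4.1 compares groups at baseline with t-tests or Mann-Whitney tests. A group effect averaged over both visits would arise only as a by-product of the ANOVA. This limits the weight of the 11 to 13% figure.

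**Conclusion.** The categorical part holds as written: chi-square and Fisher's exact test are invalid for comparing the same patients at two times. How far a p-value moves depends on the data; the shift from 0.022 to 0.150 or 0.201 rests on assumed counts.

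The continuous part holds only as an ambiguity to be removed. The losses calculated (SE of change 1.4 to 1.8 times too large, power 51% or 22% instead of 80%, group-effect type I error 11 to 13%) need both the literal unpaired reading and an assumed correlation of 0.5 to 0.7. Under a repeated-measures reading they are zero.

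The point covers visit-to-visit comparison of vascular, cognitive, circulating and MRI measures. Section 2.7 counts neurovascular coupling and WMH in the primary outcome, so a reader might conclude that the primary longitudinal result is compromised. The documents do not support that, because that result comes from logistic regression with one outcome per patient. This is a correction worth making before analysis, not a flaw in the main test.

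**What to change.** Amend the opening of section 4.2:

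- **Categorical, within group:** use McNemar's test for binary measures. For Fazekas grade use the Wilcoxon signed-rank test, the Stuart-Maxwell test or an ordinal mixed model. For MRI measures, say that the first time point is the scan at MCI diagnosis.
- **Categorical, between groups at one time point:** keep chi-square or Fisher's exact test.
- **Continuous:** state that a repeated-measures ANOVA or linear mixed model will be used, with visit as a within-participant factor and a group-by-visit term. Naming the factor is enough to remove the ambiguity; the mixed model is an option, not a necessity.

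The cost is wording only. No new data are needed, and follow-up is expected to run to 2026 (section 3.7).

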## 2. Study aims and protocol

### 2.1 Study aims

To determine whether history of COVID-19 infection in patients with MCI disrupts systemic endothelial function and impairs NVC response compared to MCI patients with no history of COVID-19 infection.To determine whether history of COVID-19 infection aggravates the impairment of fluid cognitive abilities in patients with MCI.To determine whether impairment of NVC responses in recovered COVID-19 patients with MCI contributes to increased conversion of MCI to dementia.To determine whether COVID-19 related increases in white matter hyperintensity (WMH) burden contribute to conversion of MCI to dementia.

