### 2.10 Data collection process

Patients who have consented to the study are interviewed for demographic information (sex, age, race education), COVID-19 history (symptoms during infection, and symptoms without confirmed infection), COVID-19 vaccine history, medical history (oncological, genitourinary, gastrointestinal, respiratory, endocrine, neurological, cardiovascular, musculoskeletal, and psychological conditions), screened for DVA (eye surgery history, photosensitive epilepsy, glaucoma, allergies to tropicamide), and social history (previously or current use of tobacco, alcohol, and recreational drugs, and adverse childhood experiences). Medication list is obtained from all patients, and common age-related conditions (i.e., hypertension, diabetes) must be pharmacologically controlled. All patients enrolled have baseline MRI data with neuroradiologic report at MCI diagnosis. Every 6 months patients have repeat neurocognitive screening and evaluation through OUHSC Department of Neurology faculty to identify if patients have progressed from MCI to dementia. Physiologic, circulating factors, and cognitive data is obtained from patients at visit one and at 18-month follow-up. Patients are scheduled through the Department of Neurology for a second MRI to obtain neuroradiologic report at 18-month follow-up after visit one.

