#### 3.1.2 Neuroimaging investigations

Prior to visit one, patients were diagnosed with MCI and neuroradiologically (i.e., MRI) assessed for small vessel complications. In a recent meta-analysis from Guo and Shi, small vessel ischemic damage to the brain, evidenced by white matter hyperintensities (WMH) on MRI, was associated with increased risk of development of MCI and dementia [50]. Ischemia localized to, and originating from small vessels, and microbleeds are two common pathologies in cerebral small vessel disease (CSVD) [51], and can be imaged by MRI through T2 fluid attenuated inversion recovery (FLAIR) and T2* gradient echo (GRE) or susceptibility weighted imaging sequences (SWI), respectively. All study participants, in addition to the first MRI scan performed as a point of care before enrollment into the study, will be neuroradiologically evaluated at Visit 2 using a 3T MRI. Increased burden of WMH (i.e., confluence of deep foci and extension of periventricular WMH into the deep white matter) are one of the most common manifestations on T2 FLAIR MRI imaging for diagnosis of CSVD [52] and is associated with acute and recovered COVID-19 patients [22]. Moreover, burden of WMH, determined by Fazekas scale [53], will be longitudinally assessed as a contributing factor for conversion of MCI to dementia in COVID-19 patients. The Fazekas scale grades the periventricular and deep white matter from 0–3, depending on the size and confluence of the lesions [53,54]. This grading system is the most widely used system to date to identify severity of white matter pathology [53,55]. Additionally, presence of microbleeds will be neuroradiologically assessed, as this pathology is also associated with COVID-19 and has a specific pattern of distribution that distinguishes CSVD burden in recovered and acute COVID-19 patients from other known causes (i.e., hypertension, acute respiratory distress syndrome) [22].

WMH burden will be evaluated at baseline by Fazekas scale to determine if there are differences at diagnosis that could influence results at cross-sectional cognitive and physiological measurements. Longitudinally, WMH burden will be calculated at 18-months to determine the influence of WMH on progression to dementia and whether COVID-19 increases burden of WMH in patients with MCI.

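### Change in WMH burden runs to the month-18 MRI, past most expected dementia diagnoses, so the primary model cannot show that it contributes to conversion

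*Protocol article*

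**What the plan says.** The fourth aim (Section 2.1) is "To determine whether COVID-19 related increases in white matter hyperintensity (WMH) burden contribute to conversion of MCI to dementia". Section 4.2 makes this part of the primary longitudinal question: "we will determine whether COVID-19 related impairment in NVC and increases in WMH burden contributes to progression to dementia". On the model it says "multivariate analysis will be conducted to determine the effect of COVID-19, NVC (i.e., fNIRS), change in WMH burden", and it adds interactions of group with neurovascular coupling (NVC) and WMH burden. The abstract names the method: "Multiple logistic regression will be used for primary longitudinal data analysis". Table 1 lists progression as a binary variable.

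WMH is graded on the Fazekas scale (0–3) at two times. Section 2.7 places the first at MCI diagnosis, before the pandemic, and the second at 18 months. Section 3.1.2 gives the purpose of the second reading: "Longitudinally, WMH burden will be calculated at 18-months to determine the influence of WMH on progression to dementia".

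Conversion is sought more often. Section 2.10 says "Every 6 months patients have repeat neurocognitive screening and evaluation", and Section 2.2 says "Study participants will undergo semi-annual clinical neurologic evaluations as a part of standard care". No MRI is tied to a dementia diagnosis. Section 2.2 offers an early termination visit with the Visit 2 evaluations, but leaving the study triggers it, not conversion.

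**The concern.** A contributor to an event has to come before it. Here the explanatory variable is complete only at month 18, while the event may have been diagnosed at month 6 or 12. Logistic regression on a binary outcome ignores when the event happened, so the model treats change before and after the diagnosis alike. If WMH accumulates faster once a patient has dementia, the coefficient becomes positive even when WMH played no part in the conversion. The group-by-WMH interaction uses the same readings and has the same weakness.

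At stake is one arm of the study's proposed mechanism: that COVID-19 promotes white matter damage, which in turn promotes dementia. An analysis plan could not recover the order from these two scans. It could only change the predictor or the claim.

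**Working it through.** **Inputs.** Conversion rates of 10/18 (55.6%) with COVID-19 and 23/100 (23%) without, dropout up to 10% and up to 200 patients (all Section 2.4); two MRIs (Sections 2.7, 2.10, 3.1.2); 6-monthly evaluation (Sections 2.2, 2.10). As a check on the rates, the stated p = 0.011 reproduces with the continuity-corrected chi-square (0.0108).

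**Step 1: part of the change that follows diagnosis.** Let L be the months from the first MRI to Visit 1, and d the month of diagnosis. The share of the change interval after diagnosis is (18 − d)/(L + 18). The documents do not give L, so a range of 0 to 36 months is assumed.

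| Diagnosed at | Months after diagnosis | Share, L = 0 | Share, L = 36 |
|---|---|---|---|
| Month 6 | 12 | 12/18 = 67% | 12/54 = 22% |
| Month 12 | 6 | 6/18 = 33% | 6/54 = 11% |
| Month 18 | 0 | 0% | 0% |

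**Step 2: how many conversions are affected.** With 18-month risk p and a constant hazard, the share diagnosed by month 12 is [1 − (1 − p)^(2/3)]/p.

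- Without COVID-19: (1 − 0.77^(2/3))/0.23 = 0.160/0.23 = 70%.
- With COVID-19: (1 − 0.444^(2/3))/0.556 = 0.418/0.556 = 75%.

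This takes the Section 2.4 rates as 18-month risks and assumes that the clinic visits fall at months 6, 12 and 18 from Visit 1.

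**Step 3: what it could do to the test.** Trials were simulated in which WMH had no effect on conversion.

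*Standardised change.* 180 patients (200 × 0.9), 1,000 trials, logistic regression on COVID status and WMH change. The score is continuous, and WMH grows by an extra g SD per year after diagnosis (g is assumed).

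| g (SD/year) | p < 0.05, groups 1:1 | p < 0.05, groups 18:100 | Odds ratio per SD |
|---|---|---|---|
| 0 | 4% | 4% | 1.0 |
| 0.25 | 13% | 13% | 1.16 |
| 0.5 | 41% | 36% | 1.33 |
| 1.0 | 91% | 85% | 1.7 |

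*Fazekas-type change.* 164 completers (assumed), 28% converting (33/118), and an assumed mean change of 0.4 grade with SD 0.5 per 18 months.

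| Setting | Growth doubles | Growth triples |
|---|---|---|
| First MRI at Visit 1, continuous score, faster growth from diagnosis | 35% | 88% |
| First MRI 36 months earlier, whole grades, faster growth from diagnosis | about 6–12% | about 11–28% |
| First MRI 36 months earlier, change rounded to whole grades with no 0–3 ceiling, faster growth from the true conversion time | 22% | 70% |

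The ranges in the second row reflect how the spread of change is assumed to grow with the interval. With no acceleration, every setting gives about the nominal 5%.

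**The case against.** The strongest reply is that the first MRI precedes Visit 1, perhaps by years, so part of the change precedes every conversion and possibly most of it. This stands. It rules out saying that the predictor as a whole follows the outcome. It also means that patients first diagnosed at month 18 are little affected, since their change has largely accumulated beforehand. It does not restore order for those diagnosed earlier.

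A second reply is that the bias is hypothetical. This also stands in part: no growth rate after diagnosis is documented, and coarse grading with a long interval shrinks the effect. A reader might infer from the larger simulated figures that a false positive is likely. The documents do not support that.

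A third is that the authors already hedge. Section 1 speaks of examining correlation, and Section 5 concedes limited capacity to establish causation. But that concession concerns confounding between COVID-19 and conversion, not the order of WMH change and conversion, and Sections 2.1 and 4.2 keep the language of contribution.

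A reader might extend the point to NVC. The text does not support calling that an error. fNIRS is recorded at Visit 1, before any follow-up conversion. Section 4.2 does not say which fNIRS value enters the model, but that is detail an article may leave to the full plan.

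**Conclusion.** The point holds as a limit on what the primary model can show. For roughly 70–75% of expected conversions, WMH change before and after diagnosis is mixed in one number that two scans cannot split. The model therefore cannot support the conclusion that WMH increase contributes to conversion. That share rests on a constant hazard, the Section 2.4 rates read as 18-month risks, and visits at months 6, 12 and 18.

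It is not shown that WMH change follows dementia in this population, nor that the type I error is inflated by any particular amount. Inflation is absent without post-diagnosis acceleration. If there is acceleration, the size depends on its rate, the time from first MRI to Visit 1, and the Fazekas grading. The plan should be changed because the remedy is cheap and the claim belongs to the primary outcome.

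**What to change.** In Section 4.2:

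1. Base the conversion model on COVID status and predictors measured before the outcome: the pre-enrolment Fazekas grade and the Visit 1 fNIRS coefficient.
2. Analyse WMH change as an outcome of COVID status in its own model.
3. Report the link between WMH change and conversion as an association without temporal order. Add a sensitivity analysis restricted to non-converters and patients first diagnosed at month 18.

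Align the wording of Aim 4 and Section 2.7 with this.

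**Cost.** Wording only, with no new data. The Aim 4 statement on WMH increase becomes an association. The pre-enrolment grade does not replace it, because a scan from before the pandemic cannot carry a COVID-related increase. The sensitivity analysis has few events: with 180 patients, about 180 × 0.280 × 0.298 = 15 month-18 conversions at the pooled rate, or 180 × 0.393 × 0.280 = 20 with equal groups.

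Bringing the second MRI forward to the diagnosis visit is not recommended. Scan timing would then depend on the outcome, giving converters shorter intervals than non-converters.
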